## Introduction

Primary care plays a crucial role during the COVID-19 pandemic [1, 2].

While hospital care and the concern around potential insufficient intensive care resources were very much a focus in the earlier stages of the pandemic, it was the GP practices who usually (and, again, were) the first point of contact for the patients. Practices often had to decide who needed hospital care; they also provided and monitored patients with COVID-19 at home while providing continuous care for all other patients [3–5].

In Germany, 80 to 85 percent of the patients suffering from Covid-19 received medical care in the ambulatory care sector [6]. Important characteristics of the German health care system as a framework for GP practice organization are described in Box 1.

Box 1. Characteristics of the German health care system as a framework for GP practice organization
Generally
lack of a gatekeeping system;important role of self-governing bodies [7, 8].
General practitioners
are on average responsible for 2,000 inhabitants;see on average 242 patients per week, with an average consultation time of 7.6 minutes;are usually self-employed and work in large part in a single-handed practice;usually rely on a personal communication infrastructure with colleagues, other specialists, and nursing facilities;largely decide autonomously about staff, working hours, and the organization of their practices [7, 9].
Medical practice assistants
(also called health care assistants, or “Medizinische Fachangestellte” in German)work under the legal responsibility of the GPs;go through a three-year vocational training program;are qualified for office and management duties as well as basic clinical tasks, such as measuring blood pressure and taking blood samples;may take over additional tasks including injections, vaccinations, or home visits, according to the “Agreement on the delegation of medical services to non-medical staff in ambulatory healthcare” [10–12].

The pandemic resulted in several spontaneous and unsystematic changes in the supply and uptake of health care services, affecting general practitioners (GPs), medical practice assistants (MPAs), and their patients [13, 14].

The idea for the study protocol presented here was developed in a practice advisory board meeting of the practice-based research network RESPoNsE (for details on RESPoNsE, see Box 2).

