Even though the MPAs in Germany also play a crucial role in meeting the new challenges in German GP practices, there have been only few reports on their perspective from early phases of the COVID-19 pandemic, in which concerns are described regarding the uncertain course of the pandemic, worries and a high level of responsibility for the wellbeing of their patients, fear of contracting COVID-19, and a general feeling of not being properly prepared for the challenges of the pandemic, including the necessary organizational adaptations [34, 35]. While, at the beginning of the pandemic, the focus of public interest and reporting was on the situations of intensive care units and the working conditions for hospital nurses [36], only recently have MPAs received more public attention toward the burden they bore [37].

From the beginning of the pandemic, utilization of health care for non-urgent needs declined [38]. Due to a fear of contracting COVID-19, patients avoided medical care wherever possible [39], sometimes with severe consequences, including death from strokes, heart attacks, cancer, and other acute illnesses [40–42]. A longitudinal online-based patient survey could show that, from the perspective of the patients, the supply of medication has broadly not been impaired, but also revealed that it was considerably more difficult to get an appointment with the GP, with results differing according to which phase the pandemic was concurrently in [43]. In the first six months of the pandemic, in particular, patients postponed regular health checks and routine vaccination appointments [44].

At the same time, mental exhaustion, anxiety, and feelings of loneliness and isolation increased among the general population, adding to the challenges faced by GPs and MPAs during the pandemic [45].

For all three groups, the COVID-19 pandemic may change the general view on the appropriateness of care. Before, there was only limited awareness of unnecessary care [46]. Now (during the pandemic) health care providers, and patients had to decide intuitively and without clear guidance or evidence which medical services were truly necessary [14, 47].

Therefore, the pandemic may also provide the opportunity to revisit health care practices that may not be effective or efficient [13, 48].

It is the subjective experience during the pandemic from the three groups involved (GPs, MPAs, and patients) that most likely will shape the future health care landscape.

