## Methods

### Aim

This study addresses the following research question:

What are the views of GPs, MPAs, and patients on the provision and utilization of health services during the COVID-19 pandemic? With particular regard to:

aspects of underutilization/undersupply of regular care for non-Covid related conditions;requirements, practicability and sustainability of adjustments to practice organization and management (for example virtually-delivered care); andthe appropriateness of regular care services that may have seemed dispensable under pandemic conditions

Furthermore, the three groups involved (GPs, MPAs, and patients), will have the opportunity to express other aspects or concerns experienced during the COVID-19 pandemic.

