	Requirements/resources in order to maintain health care provision during the pandemic (for example, material, qualification, information).	strongly agree–agree—neutral- disagree -strongly disagree
	*Example statement*: *“In order to maintain the provision of care under pandemic condition we need … better qualified personnel”*	
GPs only	Subjective assessment of usefulness of information by different professional associations and organizations during the pandemic (for example, the General Medical Council, Standing Committee on Vaccination, Federal Centre for Health Education, German College of General Practitioners and Family Physicians).	Very helpful–rather helpful–neutral–rather not helpful–not helpful at all –don´t know
	*Example statement*: *“How would you assess the information given during the pandemic by the… German College of General Practitioners and Family Physicians“*	
MPAs only	Personal anxieties and concerns during the pandemic (for example, stress, risk of infection and health issues, social conflicts, economical burdens).	strongly agree–agree -neutral- disagree -strongly disagree
	*Example statement*: *“What are the primary issues of fears and worries for you during the pandemic… constant stress “*	

Participating GPs and MPAs will be asked to fill in a second questionnaire after 12 to 18 months. In this way, we will explore which views and possible changes in health services persist over time. As the questionnaires will be anonymous, the comparison will be made on an aggregated level.

The GPs who participated in the first survey will also be asked to cooperate in the patient survey. Those who indicate an interest on the response form will be contacted again with further information on the proceedings and will be asked to consent into participating in the study. From a previous study (not yet published), we expect about 50 to 100 GPs to take part in this portion of the study. Participating GPs may indicate whether they expect to successfully distribute questionnaires for 50 or 100 patients during the standardized study period of four weeks. Questionnaires will be sent to the practices accordingly to be distributed among patients who sit in the waiting room. Patients will be provided with information on the study, asked to fill in the questionnaire anonymously, and to place it in a pre-prepared box. After the given study period, the practice team will send back the questionnaires using a prepaid envelope.

Inclusion criteria are:

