At least 18 years old or moreAble to read and fill out a German questionnaire

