### Outcomes

The primary outcome is that the views of GPs, MPAs, and patients be obtained, on the supply and utilization of health services during the COVID-19 pandemic, addressing positive as well as negative aspects, such as:

aspects of underutilization/undersupply;possible identification of services that turned out not to be necessary;unanticipated benefits like improvement of organizational matters and use of virtually-delivered care.

Piloting the structural development of the network, secondary outcomes are the number of participating GPs and MPAs and the number of participating patients. The number of participating GPs will be compared in terms of whether or not they are members of RESPoNsE.

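### The patient survey recruits only in waiting rooms, so patient-reported underutilization and virtual-care use describe current attenders, with a selection bias of uncertain direction

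*Protocol article*

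**What the plan says.** The protocol article, under Quantitatively: Surveys, gives one route into the patient survey. GPs who took part in the first survey and express interest are contacted again, and "we expect about 50 to 100 GPs to take part in this portion of the study". The volume per practice is set in advance: "Participating GPs may indicate whether they expect to successfully distribute questionnaires for 50 or 100 patients during the standardized study period of four weeks". Then: "Questionnaires will be sent to the practices accordingly to be distributed among patients who sit in the waiting room". Eligibility asks only for adult age and the ability to complete a questionnaire in German.

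No mailed, list-based or remote route to patients is described. The interviews are with GPs and MPAs. The two patient focus groups were drawn from the patient advisory board and served to develop the questionnaire (Qualitatively: Focus groups and interviews).

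The first item listed under Aim is "aspects of underutilization/undersupply of regular care for non-Covid related conditions", and virtual care is given there as an example of practice adjustment. Under Outcomes, "The primary outcome is that the views of GPs, MPAs, and patients be obtained, on the supply and utilization of health services"; underutilization and the use of virtual care are both listed as aspects. The section on integration and triangulation plans to compare results between the three groups where applicable. The Limitations discuss pandemic phase, region and low GP response. They do not discuss how patients are selected.

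**The concern.** Presence in the waiting room is itself a form of utilization, so the patient sample is selected on something close to what it is meant to describe. The Introduction supplies the reason for worry: "Due to a fear of contracting COVID-19, patients avoided medical care wherever possible". A person still behaving that way has no chance of receiving a questionnaire. Neither has a person whose only contact in the four weeks is by telephone or video. Someone who attends rarely has a smaller chance than someone who attends often.

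Two results are at stake. The first is any patient-reported frequency of postponed or missed care, or of virtual-care use. The second is the comparison between groups: GPs and MPAs report on the practice as a whole, while patients report as current attenders. A gap between them could come from sampling rather than from differing views.

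**Working it through.** The article states no underutilization rate, sample size or precision target for patients, so there is no figure of the plan to reproduce. The calculations show how far, and in which direction, attendance-based selection can move a proportion. All rates below are assumptions.

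**1. Volume and sampling error.** Inputs from Quantitatively: Surveys are 50 to 100 GPs and 50 or 100 questionnaires each.
- Questionnaires: 50 × 50 = 2,500 up to 100 × 100 = 10,000.
- 95% half-width at an assumed 30%, with full return and clustering by practice ignored: 1.96 × √(0.3 × 0.7 / n). This is 1.8 points at n = 2,500 and 0.9 points at n = 10,000.

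**2. Effect of relative attendance.** Let p be the true share who underused care, and r their chance of being in the waiting room relative to other patients. The observed share is p·r / (p·r + 1 − p). With p = 30%:

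| r | Observed share |
|---|---|
| 0 | 0% |
| 0.25 | 0.075/0.775 = 9.7% |
| 0.5 | 0.15/0.85 = 17.6% |
| 0.75 | 0.225/0.925 = 24.3% |
| 1 | 30% |
| 1.5 | 0.45/1.15 = 39.1% |

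The shift does not depend on n. At r = 0.5 it is 12.4 points, against a sampling error of at most 1.8 points.

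**3. Does the direction follow from visit frequency?** Assume 60% low users (0.1 visits per four weeks) and 40% high users (0.6 visits).
- Chance of at least one visit, 1 − exp(−rate): 0.095 and 0.451.
- Low users' share of the sample: 0.6 × 0.095 / (0.6 × 0.095 + 0.4 × 0.451) = 0.24.
- If 40% of low and 20% of high users postponed care: true 0.6 × 0.4 + 0.4 × 0.2 = 32%; observed 0.24 × 0.4 + 0.76 × 0.2 = 24.8%. This is 7 points too low.
- With those two percentages swapped: true 0.6 × 0.2 + 0.4 × 0.4 = 28%; observed 0.24 × 0.2 + 0.76 × 0.4 = 35.2%. This is 7 points too high.

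The sign depends on whether rare or frequent users postponed more, and the document does not say.

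**4. Would weighting help?** Weight the same sample by inverse visit rate. Low users' weighted share is (0.24/0.1) / (0.24/0.1 + 0.76/0.6) = 2.40/3.67 = 0.65.
- First case: 0.654 × 0.4 + 0.346 × 0.2 = 33.1%, against a true 32%.
- Swapped case: 0.654 × 0.2 + 0.346 × 0.4 = 26.9%, against a true 28%.

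The error falls from about 7 points to about 1 in either direction. This holds only if visit frequency is reported accurately and drives selection. People with no visits get no weight because they are not in the sample.

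**The case against.** A reader might infer that underutilization is measured only in the waiting room. It is not. Table 3 shows that the GP and MPA questionnaires ask how the frequency of visits, home visits, routine checks, vaccinations and telephone or video care changed, and about practice visits by chronically ill patients. None of those answers depends on which patients are present. They are providers' perceptions, however, and cannot stand in for the views of absent patients.

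A reader might also infer that the primary outcome as a whole is biased downward. The document does not support that. The outcome is a descriptive collection of three groups' views in an explorative study, with no single underutilization estimate. The direction is also open: the survey is retrospective and takes place more than two years into the pandemic. Former avoiders who have returned can be sampled and can report what they postponed, and catch-up visits could over-represent them.

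Box 1 says GPs "see on average 242 patients per week, with an average consultation time of 7.6 minutes". Four weeks then give 4 × 242 = 968 contacts, of which 50 or 100 questionnaires are 5.2% or 10.3%. This is a sampling fraction, and a low one is not a bias. Nor does the article say that staff choose whom to ask; hand-out instructions are a detail that it may leave to the full protocol.

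The patient questionnaire is not shown, and changes in utilization were a focus-group theme, so a visit-frequency item may already exist. Finally, Table 2 openly describes the source as patients of participating practices, a pragmatic frame for an anonymous survey.

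These arguments narrow the point but do not remove it. The only patient route is selected on attendance, and the Limitations do not say so.

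**Conclusion.** The point holds for the patient component of the primary outcome and for its comparison with GP and MPA reports. Persistent avoiders and telephone- or video-only users cannot enter, and infrequent attenders are under-sampled. Under the assumptions shown, the distortion ranges from several points to more than ten and can exceed sampling error many times over. It is plausibly downward if avoidance persists. It could be upward if former avoiders are catching up or if frequent users postponed more. The sizes are illustrations, because the document provides neither p nor r. This is a should-fix point, held with moderate confidence.

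**What to change.** 1. Make sure the patient questionnaire asks for the number of practice contacts in the last 12 months, separately for in-person visits (counting the present one) and for telephone or video contacts. Study status lists the patient survey as still to be prepared. Because responses are anonymous, this information cannot be recovered from respondents later.
2. Report the patient utilization items unweighted and, as a sensitivity analysis, weighted by the inverse of in-person visit frequency. A 12-month count only approximates the chance of attending in the four-week window, so a recent surge of catch-up visits would be only partly corrected.
3. Word the patient conclusions as applying to current attenders of participating practices, including where they are set against GP and MPA answers.
4. Add attendance-based selection to the Limitations, with its direction described as uncertain.

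The cost is one extra item, one further analysis and a few sentences. Weighting will widen the intervals, and complete non-attenders will remain unobserved whatever is done within this design.

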### Qualitatively: Focus groups and interviews

Two focus groups with members of the patient advisory board were performed to develop the patient questionnaire. The format for the groups was based on a semi-structured focus group discussion guide, building on preliminary discussions with the patient and practice advisory board and a literature search, as knowledge bases.

The focus groups were conducted using an online format, and were recorded, transcribed verbatim, and analyzed thematically using a combined deductive-inductive approach.

Emerging themes were:

Changes to utilization and perceived changes of provision of health services in a GP practice.Perceived roles of GPs and practice teams during the pandemic.Information needs during the pandemic and perceived quality of information given by GPsConcerns and fears during the pandemic.

Qualitative interviews with GPs and MPAs will be performed after the GP and MPA-questionnaires are analyzed and will provide a more in-depth exploration of some aspects of the questionnaire.

GPs and MPAs who indicated their interest are eligible to take part in the interviews. There are no exclusion criteria. We aim to conduct 15 to 20 interviews in each group or until thematic saturation is reached independently of both groups, using a new information threshold of <5% [58]. Purposive sampling will be applied if more than 20 GPs and 20 MPAs are interested in taking part in this study [59]. All interviews will be held by the same member of the research team and will last 30 to 40 minutes.

The semi-structured interview guide is developed according to the framework by Kallio et al and will build on the preliminary discussions with GPs and MPAs, results of the questionnaire and a literature search as knowledge bases, building a preliminary interview guide addressing main themes and using follow-up questions, performing internal testing and field testing in a pilot phase and finalizing a complete semi-structured interview guide [60].

It may include the following aspects:

Lessons learned / best practice modelsIdentified support needsChallenging situationsSustainability of changes in provision and organization of care during the pandemic.

Interviews will be audio-recorded and transcribed verbatim. Any identifying details will be removed. Written informed consent will be obtained in advance.

### Mixed methods: Integration and triangulation

In this study, different perspectives, methods, and time points have to be combined and integrated in a meaningful way. Integrating Quantitative and Qualitative Methods has a long tradition in primary care studies [61, 62].

We draw on the definition of Johnson et al. for mixed methods research: “Mixed methods research is the type of research in which a researcher or team of researchers combines elements of qualitative and quantitative research approaches (e.g., use of qualitative and quantitative viewpoints, data collection, analysis, inference techniques) for the broad purposes of breadth and depth of understanding and corroboration” [63].

The purposes of our mixed method approach are development and complementarity, using a convergent design and building on the notion from Creswell and Plano Clark that a mixed methods design should be labelled according to the intent of the design [64–66] (Fig 2).

**Fig 2 pone.0279413.g002:**
[figure not shown]
Mixed methods design.

Integration will use triangulation methods [62] and will address:

The perspective of the members of the research team (Investigator-Triangulation):

The research team consists of two senior researchers who are GP and have a long-standing experience in qualitative and quantitative research, a junior researcher who is in training as a GP and has a qualification in qualitative methods, health care scientists with experience in qualitative and quantitative research (one of them with a background in nursing) and of the members of the practice advisory board who are GPs or MPAs in Berlin and Brandenburg. Quantitative analysis will be supported by biostatisticians. Every step of the study will be discussed within the research team to integrate the different perspectives and backgrounds, with the aim of reducing observer bias.

The perspective of the three groups involved and different time points for two of the groups (Data-Triangulation):

The three groups (GPs, MPAs, and patients) were involved in the development of the research question and/or the identification of themes to be addressed in the study. The results of the study portions will be compared between the groups, where applicable. For GPs and MPAs, the results of the questionnaire will be compared over two points in time.

The quantitative and qualitative components (Between-method-Triangulation):

The qualitative and quantitative study parts are performed sequentially. The patient survey focus groups with patients are conducted before performing the questionnaire with patients (exploratory), and the qualitative interviews with GPs and MPAs are following the quantitative survey (explanatory).

Integration will take place when the results of the questionnaire lead to decisions about the interviews guide (GPs and MPAs), when the development of the patient questionnaire is based on the results of the focus groups with patients, and when the results are interpreted and compared between the study parts and between the groups. We adopt a model that relies on the principle of complementarity; using the strengths of one method to enhance the other [67].

We anticipate the possibility of conflicting findings between the surveys and interviews. This is to be expected to some extent simply because the methods are very different. By using the framework of Moffat et al., we will not use the results of the two methods for cross-validation purposes but will consider them to be complementary [67]. We will compare the demographic characteristics of the samples for differences. We will also critically appraise the use of quantitative measures. While qualitative interviews have the potential to explore some issues in greater depth than a quantitative questionnaire, they could also reveal some misunderstanding of the survey questions.

